##### Secondary analysis

Univariate Poisson regression with the same outcome will be used to evaluate associations with other variables: iron status at baseline, breast-feeding, age, gender and use of bed-net. These will then be introduced and re-evaluated in a multiple Poisson regression model, which will allow for adjusted group comparisons. Most importantly, by including the baseline iron status variable and the interaction with the main group variable, we can focus on the iron sufficient children that are receiving iron supplements and compare them against the others. The Poisson models will be validated by checking the model fit and for over-dispersion. Adjustments or transformations will be used if necessary.

The number of hospital admissions will be analyzed in a similar fashion, using Poisson regression. The parasite count outcome will be compared between the two groups, using a t-test. Univariate associations with other factors will be verified here as well, using t-tests, correlation coefficients and univariate regression.

Ultimately a multiple regression model will be developed, again for the purpose of adjusted comparisons between groups.

The normality of the data will be verified and, in the case of any departures, a log-transformation will be used and the data reanalyzed. If the log-transformation fails to achieve normality, a nonparametric alternative will be used instead. All statistical analyses will be carried out using SAS 9.1. The Analysis will be carried out on an intention-to-treat basis including all randomized children.

Upon the completion of the first intervention phase, an interim analysis will be performed by a Data and Safety Monitoring Committee (DSMC) as described above (primary analysis). The study will be stopped if the incidence of malaria is higher in one group.

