#### *Iron Homeostasis and infectious disease risk*

The body's ability to maintain a safe equilibrium of iron is crucial and complex. Iron homeostasis is regulated at the level of absorption, unlike other minerals that are regulated through excretory mechanisms. The human gastrointestinal tract is very sensitive to iron stores and oxygen carrying capacity and has the molecular and biochemical capacity to increase (up-regulate) absorption when iron stores are becoming depleted (or hemoglobin concentration is low), and to down-regulate absorption when iron stores are replete. In an iron deficient individual, iron absorption may be as high as 40-50%, while in an iron-replete individual, iron absorption is between 5-10%. One can imagine that humans developed this sensitive and sophisticated regulatory capacity since too little iron can lead to inadequate oxygenation of vital tissues (and ultimately death), while too much iron can overwhelm the capacity of the body to safely bind the iron to protein, leaving potentially toxic free (non protein-bound) iron. In the case of malaria, it is thought that the parasite can proliferate when there is a labile pool of non protein-bound iron available. On the other hand, it has been postulated that iron deficiency might protect the host organism through increased zinc protoporphyrin in red blood cells, which inhibits parasite haemozoin formation, similar to the mechanism of certain anti-malarial drugs (17).

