### 3.3 Significance

Overall, this investigation will provide important information on how health-related policies and programs can be improved to ensure that infants and young children in high malaria burden countries are safely protected from micronutrient malnutrition, and thus able to better achieve their growth and development potential. Specifically, the protocol will contribute the following to the literature on this topic:

1. We will determine whether the form of the iron used in the present study, and the delivery mode (powdered iron sprinkled on to food), results in an increase or decrease in malaria incidence. The Pemba study reported increased morbidity and mortality with a dissolvable iron tablet supplement which may have been rapidly absorbed from the proximal gastrointestinal tract. The form of iron to be used in the proposed study is microencapsulated ferrous fumarate, mixed in a food matrix. It is anticipated that the digestion and absorption of this form and delivery of iron is slower (lower Cmax [peak serum concentration] and higher Tmax [longer time to peak absorption]) and thus safer than a supplement.
2. As was the case in the Pemba study, we will determine whether iron replete children are more likely to have an adverse outcome, compared to iron deficient children. In the proposed protocol, we plan to enroll all otherwise healthy children without severe anemia. Based on our previous studies in Ghana, we expect that approximately 40 – 50% of children will be iron replete. Our sample size is large enough to allow for statistical evaluation of the primary outcome based on the iron status of the subjects at baseline.

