We hypothesize that the incidence of malaria will be significantly higher in children receiving iron versus a placebo of micronutrients without iron. It was decided not to use the change in anemia status as a primary outcome since, in all previous studies with powdered mineral and vitamin fortificants, anemia rates declined compared to placebo controls, or were no different from the improvement in anemia rates observed with iron drops.

Based on the 2006 estimate of “cases and deaths from fevers suspected of being malaria” for children under 5 years of age in all of Ghana (53), the baseline rate of 3.44 episodes/child/year was assumed. We estimated that a total of 351 person-years would be required to detect a 15% increase in malaria incidence rates with 80% power and at a 5% type I error. Based on the experience and expertise of the PI and co-investigator, a difference of 15% in malaria incidence was considered to be clinically significant. Knowing that all children enrolled in the trial will begin the 5-month intervention period at a similar risk level, and accounting for 15% loss to follow-up, as well as the need to test the hypothesis twice (due to the interim analysis by the Data Safety and Monitoring committee), the sample size has been calculated as 1940 children per seasonal cohort (970 per group), or a total of 3880 subjects (see Table 1 below). All calculations were reviewed by 2 statisticians who will be involved in subsequent analyses.

Table 1: Sample size calculation adjusted for testing the hypothesis twice

| Least Meaningful Difference | 2006 rates  | Adjustment for use of bed-net | Rate unexposed | Rate exposed | Person-years | Follow-up years | n          | Loss to follow-up | Sample size per group* |
|-----------------------------|-------------|-------------------------------|----------------|--------------|--------------|-----------------|------------|-------------------|------------------------|
| 0.05                        | 3.44        | 0.75                          | 2.58           | 2.71         | 3017         | 0.42            | 7240       | 0.15              | 8326                   |
| 0.1                         | 3.44        | 0.75                          | 2.58           | 2.84         | 772          | 0.42            | 1854       | 0.15              | 2132                   |

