| 0.15                 | 3.44 | 0.75                   | 2.58    | 2.97  | 351   | 0.42     | 843 | 0.15       | 970             |
| 0.2                         | 3.44        | 0.75                          | 2.58           | 3.10         | 202          | 0.42            | 485        | 0.15              | 558                    |

\*Adjusted for estimated bed net use and loss to follow-up

**5.2 Procedures***Recruitment, Randomization Process and Blinding*

Subjects will be recruited from villages in the Kintampo Health Research Centre (KHRC) study area once permission has been obtained from the village assemblies and elders, as well as the parent or guardian of the eligible child. Field researchers, employed by the KHRC, will visit individual households/compounds and interview parents or caregivers regarding the inclusion criteria. Once consent has been obtained and documented via signature or thumbprint, eligible children (one per household/compound) will be enrolled and randomized, using a computer-generated model, to either the iron (Fe) or placebo (P) group.

Sachets containing the powdered minerals with and without iron will look and taste identical with the exception that each package will be marked with an 'A' or 'B' denoting packages with or without iron. The study team and caretakers of children will be blinded to the 'A' or 'B' designation. Only the manufacturer of the powdered fortificant (in Ghana) and a research pharmacist each in Toronto and Kintampo will hold the key to the randomization and 'sachet' code lists. The key will be revealed to the 'Data and Safety Monitoring Committee (DSMC)' at the end of the first phase if a significant difference in outcomes is observed, and to the researchers after the database is closed and statistical analyses completed.

*Supply and content of the powdered mineral and vitamin fortificant.*

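### The subgroup comparison named for iron-sufficient children is not the randomised one, and the statement that the sample suffices for analysis by iron status has no calculation behind it

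*Protocol*

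**What the plan says.** Section 5.5 (Secondary analysis) first relates malaria incidence to baseline iron status, breast-feeding, age, gender and bed-net use one at a time, then jointly. It singles out one use of the joint model as the most important: with baseline iron status and its interaction with study group included, "we can focus on the iron sufficient children that are receiving iron supplements and compare them against the others". The comparator is not defined further.

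Section 3.3, item 2, puts the same aim as whether replete children fare worse than deficient children. It expects 40–50% of children to be replete and adds: "Our sample size is large enough to allow for statistical evaluation of the primary outcome based on the iron status" of the children at baseline.

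Section 3.1, on iron homeostasis, gives a reason why iron status could matter for malaria whatever sachet is given: "it has been postulated that iron deficiency might protect the host organism".

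The only sample size calculation is in section 5.1 (Sample Size and Table 1). It sizes the whole-group comparison of iron with placebo in each seasonal cohort.

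**The concern.** Only the sachet is randomised; baseline iron status is not. Taken at its word, the named comparison puts one cell (replete, iron) against three (replete, placebo; deficient, iron; deficient, placebo). The result reflects any effect of iron together with any difference in malaria risk between replete and deficient children. The framing in section 3.3 has the same feature, since it also compares across iron status rather than across arms.

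What is at stake is the reading of the replete subgroup. Sections 2 and 3.3 say that adverse effects, particularly in replete children, would call for research into screening methods before iron is given. A contrast that mixes iron with iron status could point there with no iron effect, or fail to point there when iron does harm.

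The adequacy statement matters for the opposite error. If the sample is taken to be sufficient, an unremarkable interaction test may be read as reassurance that it cannot give.

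**Working it through.** **Inputs from the protocol.** "the baseline rate of 3.44 episodes/child/year was assumed"; Table 1 multiplies this by 0.75 for bed nets, giving 2.58 per year unexposed and 2.58 × 1.15 = 2.967 exposed. Effect: "a difference of 15% in malaria incidence was considered to be clinically significant". Error rates: "with 80% power and at a 5% type I error", adjusted for "the need to test the hypothesis twice". Follow-up 5 months, 15% loss, 1:1 allocation, 40–50% replete.

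**Reproducing Table 1.** Person-years per group = (z_α/2 + z_β)² (r0 + r1)/(r1 − r0)².

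- Two-sided 5%: (1.960 + 0.842)² × 5.547/0.387² = 290.7.
- Two-sided 2.5%: (2.241 + 0.842)² × 5.547/0.387² = 352.0, against 351 stated.
- 351 × 12/5 = 842.4, so 843 children; 843 × 1.15 = 969.5, so 970.

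Table 1 therefore reproduces as 351 person-years per group, per season, with the error rate halved for two tests. Nothing in it concerns iron status.

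**The named contrast with no iron effect.** Let f be the replete share and k the replete-to-deficient malaria rate ratio. The protocol gives no value for k, so it is varied. Relative to deficient children, the comparator's mean rate is [fk + 2(1 − f)]/(2 − f), and the contrast equals k divided by that. Example, f = 0.40 and k = 1.2: (0.48 + 1.20)/1.60 = 1.05; 1.2/1.05 = 1.143. Rejection rates use a Wald test on the log ratio at two-sided 5%, mean rate held at 2.58, and 351 person-years per arm per season.

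| Assumed k | Ratio, f = 0.40 | Ratio, f = 0.50 | Rejects, one season | Rejects, pooled |
|---|---|---|---|---|
| 0.8 | 0.842 | 0.857 | 78–79% | 97–98% |
| 1.0 | 1.000 | 1.000 | 5% | 5% |
| 1.1 | 1.073 | 1.065 | 22–23% | 38–41% |
| 1.2 | 1.143 | 1.125 | 61–66% | 88–92% |
| 1.3 | 1.209 | 1.182 | 89–93% | over 99% |

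At k = 0.8 the error reverses: a true ratio of 1.15 in replete children shows as 1.15 × 0.842 = 0.97 to 1.15 × 0.857 = 0.99.

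In 1,000 simulated cohorts (one season, k = 1.2, 45% replete, no iron effect) the literal contrast rejected in 62%. Iron versus placebo within replete children rejected in 4%, and the interaction in 4%.

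**Power of the randomised contrasts.** Within replete children, SE = √[1/(2.58·PYr) + 1/(2.967·PYr)], with PYr = 0.40 to 0.50 of 351 (140.4 to 175.5) per arm per season, doubled when pooled. The interaction (1.15 in replete, 1.00 in deficient) adds 2/(2.58·PYd) to the variance, with PYd the deficient person-years per arm. Example, f = 0.40, one season: SE = √(1/362.2 + 1/416.6) = 0.0718; ln 1.15/SE = 0.1398/0.0718 = 1.945; power = Φ(1.945 − 1.960) = 49%.

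| Contrast | One season, 5% | Pooled, 5% | One season, 2.5% | Pooled, 2.5% |
|---|---|---|---|---|
| Iron vs placebo within replete, 1.15 | 49–59% | 79–87% | 38–47% | 70–80% |
| Interaction, 1.15 vs 1.00 | 32–33% | 56–57% | 22–23% | 45–46% |

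At 80% power and two-sided 5%, the detectable ratio of ratios is about 1.30 per season and 1.20–1.21 pooled.

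These figures assume pure Poisson counts and use every child. Sections 5.3 and 5.5 foresee exclusion or adjustment for CRP above 8 mg/L and a check for over-dispersion. If 20–40% were excluded for CRP (an assumption; the protocol gives no share), the pooled within-replete power at 5% falls from 79–87% to 57–79%.

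**The case against.** The strongest reply is that the sentence already specifies the right model. Status, group and their interaction separate all four cells, and iron versus placebo within replete children can be read straight from the fit. A one-cell-against-three contrast would need a single indicator and no interaction, so the phrase may be loose wording for effect modification. This largely stands. The comparator is undefined, and the three-cell reading is the literal one rather than the only one. It still leaves the protocol's self-declared most important secondary comparison described as something other than the randomised contrast.

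A reader might infer that the analysis will show harm when iron has none. The documents do not support that. Section 3.1 reports protection by iron deficiency only as a postulate, without a size. Section 8.1c contemplates higher malaria rates in anemic children who do not receive iron; anemia is not iron deficiency, but the text does not point one way. At k = 1 there is no bias, and below 1 the bias hides harm.

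A reader might also infer that the sample is too small for any analysis by iron status. That goes too far. Section 3.3 does not promise 80% power per season or for an interaction, and the pooled within-replete test of a 15% increase reaches about 80% at two-sided 5% before CRP exclusions and over-dispersion.

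Finally, this is a secondary analysis. The primary whole-group comparison is unaffected, and the protocol nowhere says that a null interaction will be taken as equal safety.

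**Conclusion.** The point holds in limited form and should be fixed, though it does not threaten the primary analysis. Followed literally, the named comparison confounds iron with baseline iron status. For assumed k of 1.1 to 1.3 with no iron effect it returns about 1.07 to 1.21, a range that includes the 15% the protocol treats as clinically significant; for k = 0.8 it turns a true 1.15 into 0.97–0.99. The size and direction rest entirely on k, which the protocol does not give. The fault is in the comparison named, not in the model.

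The adequacy statement in section 3.3 is unsupported: no subgroup or interaction calculation is shown. Of the two randomised contrasts, only the pooled within-replete test comes near 80% power for a 15% increase, and only under favourable assumptions (pure Poisson counts, two-sided 5%, no CRP exclusions). Per season, and for the interaction whether pooled or not, power is well below that.

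**What to change.** In section 5.5, replace the clause that compares replete children on iron with everyone else. State that the group-by-baseline-iron-status model will be used to estimate the iron:placebo rate ratio with 95% CI within iron-sufficient children and within iron-deficient children, together with the interaction ratio and its CI. Say whether the two seasonal cohorts are pooled for this.

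In section 3.3, item 2, replace the statement of adequacy with the power figures above and their assumptions. Say that only the pooled within-replete test reaches about 80%, and that a non-significant interaction is not evidence of equal safety.

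The cost is wording only. The model, data collection and sample size do not change; the stated adequacy becomes less favourable.

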Our secondary objectives are to determine the impact of this iron intervention on the *severity* of clinical malaria by documenting parasite counts and hospital admission rates, as well as differences in secondary complications of malaria infections, such as death, cerebral malaria, pneumonia, dehydration, and diarrhea. Although the current study is not powered to show causation between the intervention and the secondary outcomes, it is anticipated that the proposed research will help address the confusion that has been generated regarding the safe and appropriate use of iron supplements in high malaria transmission areas. If it is demonstrated that the provision of iron as a powder added to food does not have an adverse effect on malaria incidence and has a positive impact on anemia rates, then this type of iron delivery system can possibly be recommended for scale-up in Ghana and in other countries with a similar malaria burden. Conversely, if we

demonstrate adverse effects, especially in iron replete children, then further research is needed to identify inexpensive and non-invasive methods to screen children for anemia before iron is provided. **The long term goal of the proposed research is to develop new evidence to inform global policy and ultimately guide the implementation of programs to prevent and treat iron deficiency disorders in malaria endemic regions.** These goals coincide directly with the stated objectives of this RFA.

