#### *Primary and Secondary Outcomes*

The primary outcome will be **clinical malaria**, defined (according to WHO criteria) as parasitemia (malaria parasites detected on a blood smear) of any density plus history of fever (within 48 hours) or axillary temperature  $>37.5^{\circ}\text{C}$ . Criteria for clinical malaria will be taken from the UNICEF Case Management Series, entitled, "Promoting Rational Use of Drugs and Correct Case Management in Basic Health Services – Malaria Prevention and Treatment" published by UNICEF's Programme Division in cooperation with the World Health Organization in 2000. To distinguish unique malaria episodes, treatment will be supervised and follow-up blood smears will be collected from the child as described below in Section 5.2(c).

Secondary outcomes will include: (i) changes in anemia status; (ii) the severity of the clinical malaria (based on level of parasitemia); (iii) cerebral malaria; (iv) hospitalization (from any cause) (v) death; (vi) pneumonia; (vii) diarrhea and dehydration.

*Subjects/study population*

Infants and young children (6-24 months of age), living in the Brong Ahafo Region of northern Ghana, will be included in the study if, at baseline, they are ingesting weaning foods in addition to breastmilk; free from malaria or other major illness; afebrile; living in the study area for the duration of the intervention and follow-up period; and if parental consent is obtained. Inclusion of a child into the study will proceed after the possible risks and benefits are discussed with the parents (in the appropriate local language), and a signed consent is obtained. The exclusion criteria are as follows: severe anemia (hemoglobin <70g/L), weight-for-height <-3 z-score (severe wasting), kwashiorkor (defined as evidence of edema), congenital abnormality, treatment with iron supplements in the past 6 months, or any chronic illness. Children that are severely anemic (Hb<70 g/L) and/or have symptoms of clinical malaria will be excluded from entry to the study and referred to the local health provider for treatment according to Ghana Ministry of Health guidelines.

*Sample Size*

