*(c) Tracking the subjects:* All subjects who become ill and need to visit a health facility will be identified and tracked through their study identity cards. The use of such cards is standard practice at the Kintampo Health Research Centre (KHRC). If a fever has been reported or recorded, a blood sample will be taken to determine parasite species and count. If the child is admitted to the hospital or health centre, blood parasite level will similarly be determined, and further tests will be conducted (as needed) to rule out cerebral malaria, pneumonia, diarrhea, and/or dehydration. All treatments will follow the treatment guidelines in Ghana (Ghana Ministry of Health). For those assessed to have malaria, the first-line antimalarial (Artesunate-Amodiaquine) will be prescribed and provided. To determine if the treatment has been successful, and from the perspective of the study, to distinguish unique malaria episodes, treatment will be supervised and follow-up blood smears will be collected from the child on the 3rd, 7th, 14th and 28th day following treatment (this process has been successfully used in past trials including “A multi-centre, randomized, double-blind, double dummy study comparing the efficacy and safety of chlorproguanil-dapsone-artesunate versus artemether-lumefantrine in the treatment of acute uncomplicated *Plasmodium falciparum* malaria in children and adolescents in Africa Protocol #: SB-714703/005. Collaborations among KHRC/LSHTM/GSK/MMV/WHO”). All slides (with thick and thin films) will be stained with Giemsa following fixing of the thin film and read twice by independent microscopists blinded to each other’s reading. A third microscopist will be asked to read the slide if there is disagreement between the first two. The readings will be used to determine if the treatment has been successful or not.

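### Parasite count is compared by t-test with no stated unit of analysis although repeat episodes per child are expected; pooling episodes would put a nominal 5% test at about 6–11%

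*Protocol*

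**What the plan says.** Section 2 puts severity of malaria first among the secondary objectives, to be judged by "documenting parasite counts and hospital admission rates". Section 5.1 lists as a secondary outcome "the severity of the clinical malaria (based on level of parasitemia"), without saying which reading represents a child who has more than one attack.

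Section 5.2 (Tracking the subjects) says when counts arise: "If a fever has been reported or recorded, a blood sample will be taken to determine parasite species and count". The same paragraph expects repeat attacks: "to distinguish unique malaria episodes, treatment will be supervised and follow-up blood smears will be collected from the child".

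Section 5.5 (Secondary analysis) then names the test: "The parasite count outcome will be compared between the two groups, using a t-test". A multiple regression for adjusted comparison follows. Departures from normality lead to a log transformation, and after that: "If the log-transformation fails to achieve normality, a nonparametric alternative will be used instead". The over-dispersion check in that section belongs to the Poisson models.

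**The concern.** Severity is a property of an attack and is measured at each attack. The data will therefore hold several counts for many children, and counts from one child may resemble each other. A two-sample t-test and its rank-based replacement both assume independent observations. Neither fallback deals with repeat counts, because both respond only to the shape of the distribution.

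The named test is valid only if each child supplies one value, and no such value is defined. The choice is not neutral. A child's highest count, for instance, would tend to rise with the number of episodes and so mix severity with incidence, the primary outcome. Left open, the choice could be made after the data are seen.

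What is at stake is the statement that iron does or does not make attacks more severe. Section 5.8(b) also lists more severe malaria in the iron group among the grounds on which the monitoring committee may recommend ending the study after the first season.

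**Working it through.** **The plan's own figures.** The protocol gives no figure for the parasite-count comparison. The episode rate comes from section 5.1, where "the baseline rate of 3.44 episodes/child/year was assumed". Table 1 multiplies it by 0.75 for bed nets: 3.44 × 0.75 = 2.58 per child-year on placebo, and 2.58 × 1.15 = 2.967 on iron. With (z₁₋α/₂ + z₀.₈₀)²(λ₀ + λ₁)/(λ₁ − λ₀)² and two-sided α = 0.025 (inferred from the adjustment for two tests), the person-years per group are 352.0, against 351 in Table 1. The planning rate is therefore read correctly.

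**How common repeats are.** Follow-up is 5 months, so the mean number of episodes per child is m = rate × 5/12. If episodes are Poisson, the share of episodes from children with two or more is 1 − exp(−m).

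- Placebo: m = 2.58 × 5/12 = 1.075, share 66%.
- Iron: m = 2.967 × 5/12 = 1.236, share 71%.

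**Error if every episode is one observation.** The episode-weighted cluster size is E[N²]/E[N] = 1 + m. The design effect is then DE = 1 + m × ICC, where ICC is the within-child correlation of counts. The true two-sided error of a nominal 5% test is 2(1 − Φ(1.96/√DE)). The protocol gives no ICC; 0.1 to 0.5 is assumed.

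At 2.58 per year:

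| ICC | DE | Standard error too small by | True error, formula | True error, simulated |
|---|---|---|---|---|
| 0 | 1.00 | 0% | 5.0% | 5.3% |
| 0.1 | 1.11 | 5% | 6.3% | 6.9% |
| 0.3 | 1.32 | 13% | 8.8% | 9.4% |
| 0.5 | 1.54 | 19% | 11.4% | 11.4% |

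The simulation used 843 children per arm (Table 1, before loss to follow-up), normal outcomes and 4,000 runs.

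**Other rates and patterns** (errors at ICC 0.1 / 0.3 / 0.5):

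- 28 days not at risk after each episode, matching the last follow-up smear: repeat share 52%; simulated error 6.1 / 7.8 / 8.8% (3,000 runs).
- Half the planning rate, an assumed low-season value: m = 0.5375, repeat share 42%; error 5.6 / 6.9 / 8.2%.
- The site's own 7 per child-year (section 4) with the same net factor: 7 × 0.75 = 5.25, m = 2.19, repeat share 89%; error 7.6 / 12.8 / 17.6%.
- Children differing strongly in underlying rate (gamma frailty, variance 1), ICC 0.3 only: simulated error 12.9%.

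**Error with one value per child.** In the same simulation at the planning rate without a gap, ICC 0.1 / 0.3 / 0.5:

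- Child mean: 5.4 / 4.6 / 4.7%.
- First episode: 5.4 / 5.0 / 5.2%.

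The runs with the 28-day gap gave 5.1–6.1%. First episodes of different children are independent in this model, so the highest of these reflects simulation noise, not inflation.

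**The case against.** A reader might infer that the stated test is certain to give intervals that are too narrow and too many false positives. The protocol does not support that. It nowhere enters each episode as an independent observation. Randomization is by child, and the analysis set is described in terms of children. A per-child t-test fits the text as well and keeps the error near 5%. This part of the objection stands, and the inflation is conditional.

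The sizes can also be overstated. The correlation has no source in the protocol. The 3.44 rate is for fevers suspected to be malaria, while the outcome requires a positive smear, so confirmed episodes may be fewer. One cohort is in the low-transmission season, where at half the rate it is no longer true that most episodes come from children with repeats. A reader might also use 7 per year unadjusted, which gives 8.5 / 15 / 21%. That omits the net factor built into 2.58, although every household receives a net.

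A further objection is that combining several counts per child is a detail for an analysis plan. That would be fair if the protocol had left the method open. It has instead named a test and its fallbacks, and these do not fit a per-attack outcome with repeat attacks.

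The first use of the raw scale, for a count likely to be skewed, is a minor matter. Section 5.5 moves to the log scale on departure from normality. Even so, the scale of the estimate then depends on the data, whereas section 5.3 fixes log10 in advance for ferritin and ZPP/H.

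Finally, section 2 says the study is not powered for its secondary outcomes. That limits the weight of the point but does not make a mismatched test correct.

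**Conclusion.** The point holds in conditional form. The protocol names a t-test for parasite count, expects several counts per child, and leaves the unit of analysis unstated. If episodes are pooled, the true error of a nominal 5% test is about 6–11% at 2.58 per year. It is about 6–9% with a 28-day gap, 6–8% at half the rate, and 8–18% at 5.25 per year. These figures assume a within-child correlation of 0.1–0.5 and, except in the gap case, Poisson episodes. With one pre-specified value per child, or with no within-child correlation, there is no inflation.

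This should be corrected. It concerns one secondary outcome and touches neither the primary Poisson comparison nor the sample size.

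**What to change.** In section 5.5, replace the t-test with a comparison of log10 parasite density at each unique malaria episode, with the scale fixed in advance. Use a linear mixed model with a random child effect, or GEE clustered on child. State that the diagnostic count of each episode is used, not the follow-up smears. Apply the same structure to the adjusted regression. Add the first episode per child as a sensitivity analysis; a plain t-test on log10 density is valid there.

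The cost is a change of wording, slightly more analysis work, and somewhat wider intervals than a pooled t-test would show. No added visits, samples or children are needed.
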